Esketamine has irreplaceable advantages in maintaining autonomous respiration and sympathetic nervous system-like characteristics. Compared with the combination of opiates and propofol, the combination of ketamine and propofol is preferable, because the latter may increase the possibility of respiratory depression. Esketamine, the d-enantiomer of ketamine with pharmacological actions similar to ketamine’s actions and twice its action intensity provides high clearance rates and low possibility of adverse reactions, which are dose dependent [12]. Small doses of esketamine (recommended dose = 0. 15 mg/kgp [13]) can reduce tussis occurrence with good tolerability. In addition to its role in antagonising NMDAR (the n-methyl-d-aspartate receptor) widespread in the airway, throat, and lungs, esketamine directly acts on airway smooth muscles to expand bronchi through voltage-dependent L-type calcium channel and thus prevents and represses tussis reflection [14]. However, the sympathomimetic action of esketamine contributes to the transient increase in blood pressure and heart rate, whose superimposition with the endoscope insertion–stimulated sympathetic reflex exerts additional burden on the heart and is detrimental to patients with potential myocardial ischaemia [15]. However, when used in combination with propofol, esketamine can not only abolish the suppressive action of propofol on circulation and breathing but also lead to a decrease in propofol doses; thus, esketamine became increasingly popular in clinics [13]. Considering the previously reported evidence about these complementary effects of esketamine as an adjunct to propofol, the combined use of esketamine and propofol may be a promising approach that could reduce the risk of oversedation of propofol in gastrointestinal endoscopy.

Intravenous administration of lidocaine blocks the Na^+^ channel on the sympathetic cell membrane and inhibits the function of the sympathetic adrenal system, transduction of neural signals, and tracheal mechanical stimulation of the function of mucosal sympathetic receptors to prevent tussis reflection. Considerable studies have validated the efficacy of the intravenous injection of 1–2% lidocaine in anaesthesia during upper GI endoscopy; however, the myocardial depression and high individual risks of anaesthetic toxicity necessitate further explicitness of security in applications.

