
### Intervention

Figure 1 presents the study outline. The patients are selected according to their inclusion and exclusion criteria for painless upper GI endoscopy and informed consent. The patients will be divided into the four groups: P group (single administration of propofol), P + S group (administration of propofol and sufentanil in combination), P + K group (administration of propofol and esketamine in combination), and P + L group (administration of propofol and lidocaine in combination) (*N* = 100 per group). Baseline information will be collected and recorded before the operation. Anaesthetic drugs will be prepared by the nurses and anaesthetists on the day of the operation as follows: 0.9% normal saline (20 mL) for the P group, 0.5 μg/mL sufentanil (20 mL) for the P + S group as a mixture, 1.5 mg/mL esketamine (20 mL) for the P + K group, and 10 mg/mL lidocaine (20 mL) for the P + L group. Before entering the operating room, the patients will be given lidocaine defoamer for gargling to open the upper limb vein and 5 mL/min lactate Ringer solution. After entering the room, the patients will wear masks to inhale high-flow oxygen, and their vital signs will be monitored and recorded as Tire. Analgesic drugs (diluted to 20 mL according to different concentrations) prepared by the nurses will be slowly injected into their veins 5 min before examination for 30 s with the dose of millilitre 10% kg of body weight, and then, 1.5 mg/kg propofol will be intravenously administrated. Multiple-dose administration is acceptable according to the state of the patient. The endoscope will be inserted when the eyelash reflex disappeared (sedation depth grade: deep sedation). Blood pressure will be recorded after every 3 min from the beginning of the examination, and HR, SpO_2_, and RR will be recorded simultaneously. The primary outcome was the frequency of tussis, nausea and vomiting, and/or body movements observed at the insertion of the endoscope into the pharyngeal cavity or within 5 min of endoscope insertion. When subclinical respiratory depression (90% ≤ SpO_2_ < 95%) occurred, the jaw-thrust manoeuvre was performed to open the airway. When hypoxia (75% ≤ SpO_2_ < 90% for less than 60 s) occurred, in addition to the jaw-thrust manoeuvre, the oxygen flow rate was increased from 2 to 6 L/min. In case of any abnormalities, notifications should be given, and appropriate doses of propofol should be added until the endoscope exits the teeth pad. During endoscopy, 2–4 mL of propofol should be added under the conditions of extended operation time, accelerated breathing, and elevated blood pressure and heart rate to maintain deep sedation. The patients will be transferred to a recovery room after the operation, and their vital signs will be recorded after every 5 min until the patients met the standard of leaving the hospital (Steward score ≥ 4) before discharge. For each patient, the anaesthesia protocol will be completely decided by an investigator based on their experience and expertise and clinical practice guidelines. The intervention was conducted by experienced health professionals under the supervision of researcher groups. In addition, randomly check was performed to make sure the adherence of the staff to the intervention protocols. There were no concomitant interventions that are prohibited during this trial. There is no compensation or post-trial care for participants.

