### Assessments

The pain intensity, cognition function, insanity, anxiety, and depression in the patients will be assessed using a standardised and validated questionnaire. Before enrolment, the patients will be treated in anaesthesia evaluation clinics and screened according to the inclusion criteria and informed consent (Additional file 1). The demographic characteristics of the patients (age, gender, height, weight, medical history, medication history, allergy history, ASA grade, and sleep condition) will be collected, and physical characteristics, blood pressure, heart rate, and oxygen saturation of blood will be measured and recorded as Tbase. Preoperative examinations (urinalysis, haematological examination, and electrocardiogram) will be conducted to validate cardiac, liver, kidney, and coagulation functions. Pain intensity will be evaluated using the numerical rating scale. Anxiety and depression will be assessed using hospital anxiety and depression scale (HADS). Cognition function was assayed through mini-mental state evaluation (MMSE).

On the day of the operation, the vital signs, including blood pressure, heart rate, pulse oxygen saturation, and respiratory rate, will be measured and recorded when the patient entering the operating room and after induction and endoscope entrance, Afterwards, these signed will be recorded every 3 min until the patient left the room. The drug doses of anaesthesia, administration route, anaesthesia time, operation type, operation time, times of biopsy, infusion quantity, blood loss, and satisfaction of endoscopist (satisfied, average, or dissatisfied) will be documented. The vital signs of the patients in the recovery room will be recorded after every 5 min. MMSE scores will be re-evaluated before the patient leaves the recovery room, and the patients will be asked about their satisfaction degree (satisfied, average, or dissatisfied) and the operation and pain severity (0 point represents absolute no pain; 10 points denote unbearable pain). The incidence of adverse events (dizziness, headache, cardiopalmus, dyspnoea, mobility, nausea, and vomiting) will be followed up through phone calls after 0.5 h, 2 h, 1 day, 2 days, 3 days, 1 week, 1 month, and 6 months of the operation. The information about sleep conditions will be collected, and the alterations of MET scores, MMSE scores, HADS scores (the details of any specific manifestations will be inquired) will be assessed.

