### Endpoints

The primary endpoints include the frequency of tussis, nausea and vomiting, and/or body movements observed at the insertion of the endoscope into the pharyngeal cavity or within 5 min of endoscope insertion. Secondary endpoints are as follows: (1) the time of the addition of the first drug, from the end of induction to the addition of the first drug (from the injection of the study medication to the disappearance of eyelash reflex); (2) the time of recovery from anaesthesia, from the end of the operation till the patient left the recovery room (the end of operation to consciousness return); (3) perioperative propofol doses; (4) incidence of perioperative adverse events, including tachycardia, oxygen desaturation (the time of 90% ≤ SpO_2_ < 95% for more than 10 s), breathing inhibition (the time of SpO_2_ < 95% for more than 15 s), bradycardia (< 50 beats per minute or a decrease in HR of 20% or more from baseline), and high and low blood pressure (blood pressure < 30% of the basal blood pressure or systolic blood pressure or blood pressure > 30% of the basal blood pressure); (5) incidence of postoperative adverse events (within 6 months after the operation) including nausea, vomiting, increased secretion, dizziness, over sedation, infection, nightmare, uneasiness, itching, disorientation, insanity, breathing inhibition, diplopia, diarrhoea, intestinal obstruction, urinary retention, gastroesophageal reflux, constipation, shiver, and hallucination; (6) MMSE scores, MET scores, and sleep condition after 0.5 h, 2 h, 4 h, 1 day, 2 days, 3 days, 1 week, 1 month, and 6 months of the operation; (7) pharmacoeconomic outcomes (calculated incremental cost-effectiveness ratio based on cost-effectiveness analyses).

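### Secondary endpoint (4) calls an oxygen-saturation rule breathing inhibition: in patients on mask oxygen it measures oxygenation and overlaps the oxygen-desaturation item

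*Protocol article*

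**What the plan says.** In the protocol article, Endpoints, secondary endpoint (4) lists perioperative adverse events. Two of them are respiratory, and both are defined by pulse oximetry alone: "oxygen desaturation (the time of 90% ≤ SpO_2_ < 95% for more than 10 s" and "breathing inhibition (the time of SpO_2_ < 95% for more than 15 s".

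The Intervention section gives every patient oxygen from entry to the room: "the patients will wear masks to inhale high-flow oxygen". A later sentence of that section describes a flow that "the oxygen flow rate was increased from 2 to 6 L/min" when hypoxia occurs. The two descriptions of oxygen delivery are not reconciled, but on either one all patients receive supplemental oxygen.

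Respiratory rate is collected. During the examination blood pressure is taken every 3 min, and "HR, SpO_2_, and RR will be recorded simultaneously". The Assessments section says the same of the vital signs: "pulse oxygen saturation, and respiratory rate, will be measured and recorded when the patient entering the operating room", then after induction and endoscope entrance, then every 3 min.

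No endpoint or adverse-event definition in the article uses respiratory rate, apnoea or carbon dioxide. The other respiratory terms are also saturation bands. The Intervention section has "When subclinical respiratory depression (90% ≤ SpO_2_ < 95%) occurred" and a hypoxia band; the Assessments section defines insufficient oxygen supply and hypoxemia by SpO2 limits. Breathing inhibition appears again in secondary endpoint (5), for the postoperative period, without a definition.

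**The concern.** The label promises a measure of breathing, and the rule delivers a measure of oxygenation. Supplemental oxygen can keep saturation up while breathing slows, so the two can come apart in exactly the patients studied here.

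This matters because the respiratory effect is part of the case for esketamine. The Introduction states "Esketamine has irreplaceable advantages in maintaining autonomous respiration" and says that esketamine counters propofol's depression of breathing. The Discussion repeats the claim of reduced respiratory depression. A reader of the results will look to the item named breathing inhibition for evidence. Under the written rule, a difference between arms there would be a difference in desaturation, and the absence of a difference would not show that breathing was equally preserved.

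**Working it through.** The article states no figure for this item, so there is nothing to reproduce. The check is a literal reading of the rule, followed by an illustration.

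**1. Overlap of the two respiratory items in endpoint (4)**

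| Episode | Oxygen desaturation (90% ≤ SpO2 < 95%, > 10 s) | Breathing inhibition (SpO2 < 95%, > 15 s) |
|---|---|---|
| 90% to < 95% for 12 s | yes | no |
| 90% to < 95% for 20 s | yes | yes |
| wholly below 90% for 20 s | no | yes |

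Within the band from 90% to below 95%, every breathing-inhibition episode is also a desaturation episode, because more than 15 s implies more than 10 s. The second item is a longer or deeper version of the first. It is not a separate measure of ventilation.

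**2. Scoring of breathing itself (hypothetical patients)**

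| Patient on mask oxygen | Scored as breathing inhibition? |
|---|---|
| Respiratory rate 4/min, SpO2 98% | no |
| Pause in breathing, SpO2 stays at or above 95% | no |
| Respiratory rate 16/min, SpO2 94% for 20 s | yes |

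The first two rows are missed episodes under this label. The third is a saturation fall counted as a breathing event. The Intervention and Assessments sections also have staff open the airway once SpO2 falls below 95%, the same limit as the endpoint. Whether an episode outlasts 15 s therefore depends partly on how quickly staff respond.

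**3. Illustration of what missed episodes could do**

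Only the arm size, 100 per group, comes from the article. The true event rates p1 and p2 are assumed. So is the share s of true episodes that reach the SpO2 rule, taken as equal in both arms with no false positives.

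- Observed rates: s × p1 and s × p2; observed difference d = s × (p1 − p2).
- Power (two-sided 0.05) = Φ[(d − 1.96 × se0) / se1]. Here se0 = √[p̄(1 − p̄)(2/100)] and se1 = √[(a(1 − a) + b(1 − b))/100], with a and b the observed rates and p̄ their mean.

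Worked case, assumed 30% vs 15% and s = 0.5: a = 0.15, b = 0.075, d = 0.075, p̄ = 0.1125. Then se0 = 0.0447, se1 = 0.0444, and (0.075 − 1.96 × 0.0447)/0.0444 = −0.28, so power is 39%.

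| Assumed true rates | s = 1 | s = 0.75 | s = 0.5 | s = 0.25 |
|---|---|---|---|---|
| 20% vs 8% | 69% | 55% | 38% | 21% |
| 30% vs 15% | 72% | 57% | 39% | 21% |
| 40% vs 20% | 88% | 72% | 51% | 27% |

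The direction is clear: missing half the episodes halves the observed difference. The size is not, because the article gives neither the rates nor s. The s = 1 column is a ceiling. It is not the power that a respiratory-rate definition would reach, since readings every 3 min also miss episodes. The no-false-positives assumption also leaves out the third row of the table in step 2.

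**The case against.** Several points on the other side are sound.

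- **Open list.** A reader might infer that slow or absent breathing with preserved saturation goes unrecorded. The article does not support that. Endpoint (4) gives its items as inclusions, and the Assessments section gives its documented adverse events as examples. An apnoea could be reported as another adverse event, though not as breathing inhibition under the written rule.
- **Data exist.** A reader might also infer that the respiratory claim cannot be tested at all. That is too strong. Respiratory rate is recorded in all arms, the Abstract says that data on sedation-related events come from recorded vital signs, and the Statistical methodology section plans repeated-measures analysis of variance. Arms could be compared on the rate. What is lacking is a case definition that uses it.
- **Weight.** The stated hypothesis concerns tussis. The respiratory claim is rationale, no power is attached to it, and this is one component of a multi-part secondary safety endpoint.
- **Invented inputs.** The power table rests on assumed rates and shares. It cannot be presented as the loss in this trial.
- **Partial remedy.** Readings every 3 min would not catch a short, corrected apnoea. How far oxygen masks slow breathing also depends on the unreconciled descriptions of oxygen flow.
- **Consistency.** The article uses SpO2 for all its defined respiratory terms, so the choice is at least uniform.

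What survives is the mismatch between label and rule. The article states the threshold and duration outright, so this is not a detail left to a fuller document. Uniform use of SpO2 means that no defined term measures breathing.

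**Conclusion.** The point holds as a problem of definition and labelling. Followed as written, the breathing-inhibition item in secondary endpoint (4) measures oxygenation in patients on supplemental oxygen and overlaps oxygen desaturation for any SpO2 of 90% to below 95% lasting more than 15 s. It omits slow or paused breathing with SpO2 at or above 95% and includes saturation falls at a normal respiratory rate. Its evidence on the respiratory-sparing effect claimed for esketamine is therefore weak and partly misclassified, but not nil, since some breathing episodes do lower saturation below 95%.

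The conclusion rests on the text of the definition, universal mask oxygen, and the absence of respiratory rate from every definition. It does not depend on the assumed rates in the illustration, and no figure for lost power should be quoted as a finding. The primary endpoint and the sample size are untouched. This is a cheap, worthwhile improvement to a secondary safety item.

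**What to change.** In secondary endpoint (4):

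1. Rename the present item as an oxygenation event and reconcile its range and duration with oxygen desaturation and with the saturation terms in the Intervention and Assessments sections.
2. Add beside it a breathing-inhibition component based on the respiratory rate already recorded, with a limit that the investigators fix before unblinding.
3. State whether breathing inhibition in endpoint (5) uses the same definition.
4. Reconcile the two descriptions of oxygen delivery in the Intervention section, because the reading of any saturation item depends on them.

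**Cost.** No new measurement is needed. The change is to endpoint wording and the analysis listing, plus a formal amendment if it counts as a significant modification under the article's own rule. The article gives recruitment as October 2022 to April 2023 and was published in January 2024, so the data may already be collected. In that case the limit can still be set while allocation is concealed, and the report should say when it was set.

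**Downside.** Readings about every 3 min detect sustained slow breathing but miss short apnoeas, so the new component is also partial and should be reported with that limitation.

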Adverse events will be assessed and treated throughout the study. When the perioperative oxygen saturation of blood < 95%, the anaesthesiologists will raise the lower jaw and open airway; this phenomenon is defined as insufficient oxygen supply. The condition of the oxygen saturation of blood of < 90% is defined as hypoxemia. When the oxygen saturation of blood < 88%, the endoscope will be removed, and the patient will be fitted with the mask for 100% pure oxygen inhalation and respiration will be assisted using a balloon. Simultaneously, adverse events, such as cough, laryngospasm, low and high blood pressure, bradycardia, and tachycardia triggered by drugs or operation, will be documented. Postoperative adverse events, including nausea, vomiting, dizziness, oversedation, infection, nightmare, diarrhoea, insanity, blurring of vision, nystagmus, and hallucination, will be recorded in detail.

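### The respiratory events in secondary endpoint (4) need more than 10 s or 15 s of low SpO2, but airway opening starts below 95% with no stated duration, so promptly rescued episodes can meet neither definition

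*Protocol article*

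**What the plan says.** **Rescue.** The Intervention section states: "When subclinical respiratory depression (90% ≤ SpO_2_ < 95%) occurred, the jaw-thrust manoeuvre was performed to open the airway". The next step, a higher oxygen flow, also has no minimum duration, only an upper limit: "When hypoxia (75% ≤ SpO_2_ < 90% for less than 60 s) occurred". The adverse-event paragraph of Assessments states: "When the perioperative oxygen saturation of blood < 95%, the anaesthesiologists will raise the lower jaw and open airway". It adds that "this phenomenon is defined as insufficient oxygen supply" and gives SpO2 below 90% the label hypoxemia. Neither label carries a duration. Below 88%, the endoscope is withdrawn and breathing is assisted.

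**Endpoint.** Secondary endpoint (4) in the Endpoints section is the incidence of perioperative adverse events, introduced as an open list. Its two oxygenation items are "oxygen desaturation (the time of 90% ≤ SpO_2_ < 95% for more than 10 s") and "breathing inhibition (the time of SpO_2_ < 95% for more than 15 s"). The list names neither insufficient oxygen supply nor hypoxemia, and it does not name jaw thrust, raised oxygen flow, endoscope removal or assisted ventilation.

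**Who acts and who records.** Under Randomisation and blinding, the anaesthesiologist giving the sedation is blinded, and so is a second anaesthesiologist who observes and records.

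**The concern.** A duration-based event is hard to interpret when treatment designed to shorten the episode begins at the same threshold. Whether the clock reaches 10 s or 15 s then depends on three things: how strongly the drug depresses breathing, how soon the airway is opened, and how quickly saturation responds. Only the first is the quantity of interest. A patient who needed a jaw thrust and recovered in a few seconds had respiratory depression that required treatment, yet meets neither definition. Continuous SpO2 recording would not cure this, because the true duration has itself been cut short.

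The Introduction names respiratory depression as a risk of propofol and counts maintained spontaneous breathing among esketamine's advantages. The Discussion says the trial will evaluate both efficacy and safety. Endpoint (4) is where respiratory safety during the procedure is compared between the four arms, so what it counts matters.

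**Working it through.** The plan gives no figure to reproduce here: no expected event rate, and no power claim for this endpoint. The check applies the written rules to example episodes.

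**Inputs.** Rescue trigger: SpO2 below 95%, no duration stated (Intervention, Assessments). Desaturation: time in the 90–95% band above 10 s. Breathing inhibition: total time below 95% above 15 s (both Endpoints). Hypoxemia: any time below 90% (Assessments). I read the time limits as applying to a single episode.

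**Rules.** Let *b* be the seconds in the 90–95% band and *h* the seconds below 90%. Rescue is triggered if *b* + *h* > 0. Desaturation needs *b* > 10. Inhibition needs *b* + *h* > 15.

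| *b* (s) | *h* (s) | *b* + *h* | Rescue triggered | Desaturation | Inhibition | Hypoxemia label in Assessments |
|---|---|---|---|---|---|---|
| 5 | 0 | 5 | yes | no | no | no |
| 9 | 0 | 9 | yes | no | no | no |
| 12 | 0 | 12 | yes | yes | no | no |
| 16 | 0 | 16 | yes | yes | yes | no |
| 8 | 6 | 14 | yes | no | no | yes |
| 10 | 5 | 15 | yes | no | no | yes |
| 6 | 20 | 26 | yes | no | yes | yes |

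**Result.** An episode meets neither definition exactly when *b* ≤ 10 and *b* + *h* ≤ 15. This covers every episode that ends within 10 s. It also covers episodes of up to 15 s with at most 10 s in the band, so a deeper dip can go uncounted while a shallower one of similar length counts: 8 s + 6 s is missed, 12 s + 0 s is counted.

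**What this could do to a comparison (assumed figures, not from the document).** Suppose 20% of patients in each of two arms desaturate. If rescue ends 20% of episodes before the limit in one arm and 50% in the other, the counted incidences are 0.20 × (1 − 0.20) = 16% and 0.20 × (1 − 0.50) = 10%, although the true incidences are equal. If the share ended early is the same in both arms, both rates shrink by the same factor and their ratio is unchanged: with assumed true rates of 25% and 10%, the ratio stays 25/10 = 2.5. The mechanism can therefore lower all rates without distorting their ratio, or distort the comparison in either direction. The document does not say which applies.

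**The case against.** **The list is open.** Endpoint (4) covers adverse events in general and names examples, and Assessments labels these episodes without a duration. A reader might infer that every promptly rescued episode is scored as no event. The text does not support that: the episode fails the two stated definitions, but it may still be recorded under another label. What remains is that nothing says it is counted, and that the two sections define respiratory events differently.

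**Silence on duration is not a stated zero.** The Intervention section's subclinical respiratory depression uses the same band as desaturation, so the 10 s limit might be its working definition. Detection and reaction also take time. Suppose recovery after jaw thrust were exponential with mean 10 s (an assumption). Then exp(−10/10) = 37% of episodes would last beyond 10 s with no delay, but exp(−5/10) = 61% with a 5 s delay, and essentially all with a 10 s delay. The loss could be large or negligible. This stands, and it is why no loss of power should be quoted. The article claims no power for this endpoint in any case.

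**A harmful regimen could look safe.** A reader might infer this too. It would need recovery times that differ by arm, for which the document gives no evidence. The sedating anaesthesiologist is blinded, so rescue speed should not depend directly on allocation. Blinding does not, however, remove differences in how fast or how far saturation falls under each drug, or in how it responds.

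**A minimum duration has a purpose.** It screens out momentary false readings, which is reasonable when body movement is common enough to be part of the primary endpoint. Counting rescue also brings a clinician's decision into the outcome, and the Intervention section leaves the anaesthetic conduct to the investigator's judgement. Both points stand and argue for keeping the duration-only version alongside.

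**One supporting sentence is weak.** The Introduction's remark that "the latter may increase the possibility of respiratory depression" is ambiguous: by its grammar it refers to ketamine with propofol. It is not relied on here.

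**Conclusion.** The point holds as a mismatch of definitions. The rescue trigger and the endpoint share the 95% threshold, only the endpoint has a duration, and the duration-free labels in Assessments do not appear in the endpoint list. Respiratory depression that was treated promptly can fall outside both defined events, including a dip that the article itself calls hypoxemia. The endpoint as defined mixes drug effect with response to rescue and can under-count.

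The size of the under-count and the size and direction of any between-arm bias cannot be derived from the document; the 16% versus 10% example is illustration only. The conclusion rests on reading the absence of a rescue duration as written and the time limits as per episode. The primary endpoint and the sample size are not affected. The change is worth making because it is cheap, not because the trial's main conclusion depends on it.

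**What to change.** 1. Reconcile the respiratory event definitions in Intervention, Assessments and Endpoints so that each term has one meaning.
2. In endpoint (4), count a patient as having a respiratory event if the duration rule is met **or** an airway rescue is given for SpO2 below 95% (jaw thrust, raised oxygen flow, endoscope removal or balloon-assisted breathing).
3. Report the duration-only definitions separately, so that the effect of adding rescue is visible.
4. Add SpO2 below 90%, already defined as hypoxemia in Assessments, as a listed event.
5. Tabulate by arm the number of patients with each type of rescue.

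The rescue rules themselves are left as they are.

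**Cost.** Revised endpoint wording and, if the intraoperative record (not shown) lacks it, one field for the type of rescue, completed by the blinded observer already in the room. Event rates will rise in all arms, some brief or artefactual dips will be counted, and the composite will include a blinded clinician's decision. The article's planned recruitment window (October 2022 to April 2023) precedes its publication, so for patients already treated the fix works only where rescues were noted at the time. The revised definition should be fixed before unblinding and reported as a change.

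### Secondary endpoint 4 misstates its blood-pressure limits, contains a systolic term that cannot be interpreted, and names SpO2 items that miss some dips below 90% lasting more than 10 s and up to 15 s

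*Protocol article*

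**What the plan says.** All the rules in question are in item (4) of the secondary endpoints (protocol article, Endpoints), the incidence of perioperative adverse events.

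- Low and high blood pressure: "blood pressure < 30% of the basal blood pressure or systolic blood pressure or blood pressure > 30% of the basal blood pressure".
- Heart rate, in the same sentence: "bradycardia (< 50 beats per minute or a decrease in HR of 20% or more from baseline".
- Mild SpO2 item: "oxygen desaturation (the time of 90% ≤ SpO_2_ < 95% for more than 10 s".
- Second SpO2 item: "breathing inhibition (the time of SpO_2_ < 95% for more than 15 s".

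The baseline is fixed under Assessments: "blood pressure, heart rate, and oxygen saturation of blood will be measured and recorded as Tbase".

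Low saturation is also graded elsewhere. Assessments states: "The condition of the oxygen saturation of blood of < 90% is defined as hypoxemia". It then sets a rescue step: "When the oxygen saturation of blood < 88%, the endoscope will be removed". Intervention has its own band, used as a treatment trigger: "When hypoxia (75% ≤ SpO_2_ < 90% for less than 60 s) occurred". Endpoint 4 names neither hypoxemia nor hypoxia, but its event list is introduced as open-ended.

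**The concern.** The endpoint states explicit scoring rules, and two of them misclassify if followed as written.

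The blood-pressure limits are expressed as a fraction of baseline rather than a change from it. The systolic term between them has no comparator, number or unit. A scorer has to reinterpret the first and then guess or ignore the second.

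The mild SpO2 item has a floor at 90% and a 10 s threshold, while the item without a floor needs more than 15 s. Between those two durations, a shallow dip can count and a deeper dip of the same length can fail to count. The protocol itself treats the deeper dip as worse.

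This matters because the Discussion expects esketamine to offset propofol's depression of circulation and breathing. Endpoint 4 is where that expectation would be tested. Settling the definitions after the data have been seen would weaken the comparison.

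**Working it through.** The plan gives no figure to reproduce here, so the check applies the rules as written to example values. The document gives no blood pressures or event rates; baselines of 100 to 160 mmHg are assumed for illustration.

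**Blood pressure.** Let B be the Tbase value. The literal limit, for both low and high, is 0.30 × B. The limits for a change of more than 30% are 0.70 × B and 1.30 × B.

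| Assumed B (mmHg) | Literal limit | Low, as a fall >30% | High, as a rise >30% |
|---|---|---|---|
| 100 | 30 | <70 | >130 |
| 120 | 36 | <84 | >156 |
| 140 | 42 | <98 | >182 |
| 160 | 48 | <112 | >208 |

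Read literally with B = 120, readings of 70, 84 and 120 mmHg would all be high. That cannot be the intention. The bradycardia rule in the same sentence is worded as a decrease from baseline, which points to the right-hand columns.

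**Systolic term.** Two readings fit the text:

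1. It is a separate criterion whose limit is absent.
2. It names an alternative pressure to which the 30% rule applies.

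Under the first the rule is incomplete. Under the second no number is missing, but the rule does not say which pressure governs. Neither reading gives a definite limit.

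**SpO2.** For a single dip, let a be the seconds spent from 90% to <95% and b the seconds below 90%. Oxygen desaturation requires a > 10. Breathing inhibition requires a + b > 15.

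| Dip | a | b | a + b | Desaturation | Inhibition |
|---|---|---|---|---|---|
| 12 s at 92% | 12 | 0 | 12 | yes | no |
| 12 s at 85% | 0 | 12 | 12 | no | no |
| 12 s at 85%, 3 s in band | 3 | 12 | 15 | no | no |
| 12 s at 85%, 4 s in band | 4 | 12 | 16 | no | yes |
| 20 s at 94% | 20 | 0 | 20 | yes | yes |
| 20 s at 80% | 0 | 20 | 20 | no | yes |

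For b above 10 and up to 15, the dip is missed unless a > 15 − b:

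- b = 11: more than 4 s in the band is needed.
- b = 12: more than 3 s.
- b = 15: any time at all.

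At 10 s or less a 92% dip does not count either, so a dip below 90% of the same length is at no disadvantage. Above 15 s every dip counts as breathing inhibition, so 20 s at 94% and 20 s at 80% share that item. The 80% dip is then marked only by failing to meet the mild item as well.

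The 12 s dip at 85% is below the 88% level at which Assessments requires the endoscope to be withdrawn, yet it can meet neither named item.

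**The case against.** The strongest reply is that little of this would cause harm in practice. No scorer would use 36 mmHg as a limit, and blood pressure is recorded every 3 min, so events can be rescored. The SpO2 gap is narrow: a real dip to 85% crosses the 90% to 95% band on the way down and on the way up, and a few seconds there bring a 12 s dip into breathing inhibition. The open event list, and a hypoxemia definition with no minimum duration, mean that deep dips may well be recorded. The floor at 90% also matches the milder grade used under Intervention, so it looks like deliberate grading. A condensed article may leave the listing of items to a fuller document.

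Most of this stands, and it limits the point. It does not remove it. The article states these thresholds rather than deferring them, and recording an event under an open list is not the same as naming it as an item of the endpoint.

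A reader might infer more than the text supports:

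- **That a systolic cut-off has been dropped.** The term may be only an alternative reference pressure. A number lost when the text was extracted cannot be excluded either, although there is no visible gap and the other limits in the sentence came through. Nothing in the document supports a particular value, so no effect can be calculated from an assumed one.
- **That the SpO2 items miss deep dips in general.** They do so only in the duration window shown above.
- **That one arm is favoured.** Under Randomisation and blinding the recorder is blinded, so noise and missed events are more likely than a directional bias.

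**Conclusion.** The point holds in a limited form. The blood-pressure limits are misworded, with a change of more than 30% from Tbase evidently meant. The systolic term cannot be applied as written under either reading. The named SpO2 items miss a dip below 90% lasting more than 10 s and up to 15 s unless enough time is also spent between 90% and 95%, although a 92% dip of the same length counts. In longer dips they do not report <90% separately.

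The blood-pressure illustrations rest on assumed baselines, and the SpO2 results on treating each dip as a single episode. With no event rates in the document, the number of patients affected cannot be stated. The effect is confined to one secondary safety endpoint; the primary endpoint and the sample size are untouched. It should be fixed because the correction is cheap and the endpoint carries the circulatory and respiratory comparison.

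**What to change.** 1. Define low and high blood pressure as a fall or rise of more than 30% from Tbase in one named pressure.
2. Delete the systolic term, or state what it means.
3. List hypoxemia (SpO2 <90%, as Assessments already defines it) as a separately reported item of endpoint 4. Keep the two existing SpO2 items as prespecified. A 12 s dip at 85% would then be counted, under the new item.

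The cost is a rewording and one added item; nothing prespecified is removed. Blood-pressure events can be rescored from stored readings. A <90% item without a duration may pick up brief artefacts. Short dips can be recovered only if they were logged: the protocol requires action below 90% and below 88%, so staff would notice them, but logging is not guaranteed.

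Recruitment was expected to finish on April 1, 2023 and the article appeared on January 4, 2024. If the data are already unblinded, the change must be labelled as a dated post hoc clarification.
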